### Statistical analysis

As the primary hypothesis we will calculate the absolute risk differences in incidence of partial flap loss (major and minor combined) between groups. If the upper limit of the 95% CI falls within 12%, we regard this as a non-inferiority difference.

The secondary hypotheses will be tested for superiority: absolute risk difference for one or more major complications and 95% CI, and linear regression for length of stay, physical function, and blood tests.

We will perform an intention-to-treat analysis. However, since investigators can decide to withdraw a subject from the study for life-threatening medical reasons (see the subsequent section on Recruitment, consent, and withdrawal), we will perform an additional per protocol analysis and compare baseline characteristics of patients withdrawn and patients lost to follow-up. We will use multiple imputation to account for missing variables.

We will perform an interim analysis when 40 patients are randomized. If we find a significant difference through Fisher’s exact test in patients having one or more major or minor complications, we will terminate the trial. Based on previous studies, we will test our final non-inferiority hypothesis without alpha adjustment for the superiority tested interim analysis.

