### Objectives

The primary objective is to assess whether a no-dangling protocol is not inferior to a dangling protocol. Our primary outcome is measured in terms of proportion of patients who experienced partial flap loss which did not require another free flap procedure. Total follow-up for our primary objective is 6 months. Based on a rate of partial flap loss of 6%, we decided that an absolute increase in incidence of 12% would be clinically significant. We will calculate the absolute risk differences in incidence of partial flap loss (major and minor combined) between groups.

We also have the following secondary objectives:
We hypothesize that there is no difference in one or more major complications at 6 months.We would like to objectify the gaseous changes within the free flap during the dangling protocol in a select group of patients.We will measure the physical functions at 3 and 6 months and at 1, 1.5, and 2 years with the Patient-Reported Outcomes Measurement Information System (PROMIS) physical function, EuroQol five dimensions (EQ-5D), and visual analog scale (VAS) questionnaires.We hypothesize that there is no difference in the number of patients experiencing one or more minor complications at 3 and 6 months postoperatively.We will investigate whether there is a difference in the length of hospital stay between the two groups and perform a costs analysis.We will investigate infection rates and osseous union rates with a follow-up of 2 years.

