**Fig. 1 Fig1:**
[figure not shown]
Standard Protocol Items: Recommendations for Interventional Trials (SPIRIT) figure showing the phases of the trial and data collection time points

Patients in group A (dangling) at the UMC Utrecht will undergo blood tests with the use of a point-of-care testing (POCT) device. A drop of blood will be taken on a daily basis from both the flap and from the contralateral leg (control) and will subsequently be analyzed for pO2, pCO2, and pH levels. Moreover, all patients will be asked to fill out three short (PROMIS, EQ-5D, and VAS) online questionnaires at 3 and 6 months and at 1, 1.5, and 2 years postoperative. The inclusion and exclusion criteria are listed in Table 1.

**Table 1 Tab1:** Inclusion and exclusion criteria for “the dangle study”

Inclusion criteria	- Male or female
	- Age between 18 and 99 years old
	- Lower leg defect in need of a free flap reconstruction
Exclusion criteria	- Age under 18 years
	- Co-morbidities that prevent the patient from being able to undergo a dangling protocol
	- Insufficient Dutch language skills to understand the study
	- Patients who are mentally incompetent or are unable to give informed consent
	- Reconstruction with 2 or more free flaps
	- Patients who are getting a secondary free flap due to partial or total free flap necrosis

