### Point-of-care blood tests

All of the randomized patients in group A at the UMC Utrecht will undergo blood tests. Using a POCT device, a drop of blood from the free flap and from the contralateral “healthy” leg (control group) will be analyzed for blood gases (pO2, pCO2, pH). If the patient has a bilateral leg injury, the drop of blood will be taken from a different body part. This study is designed to get a better insight into the gaseous changes within the free flap during the dangling process. Blood will be taken from the free flap and the contralateral leg at the beginning and at the end of the dangling session. Table 3 illustrates the protocol for the POCT. The goal of these POCT measurements is to present a curve of the gaseous changes during a dangling protocol and to get more insight into the effect of dangling on these blood gases.

**Table 3 Tab3:** Point-of-care testing (POCT) protocol during the dangling protocol

Postoperative day	Before a dangling session	At the end of a dangling session
7	POCT from flap and contralateral leg	POCT from flap
8	POCT from flap and contralateral leg	POCT from flap
9	POCT from flap and contralateral leg	POCT from flap
10	POCT from flap and contralateral leg	POCT from flap
11	POCT from flap and contralateral leg	POCT from flap
12	POCT from flap and contralateral leg	POCT from flap

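### The superiority rule for secondary outcomes does not fit blood gases that are sampled in one arm only, and cannot support the no-difference hypotheses on complications

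*Protocol article*

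**What the plan says.** One sentence in the protocol article's Statistical analysis section sets the rule for the secondary outcomes: "The secondary hypotheses will be tested for superiority: absolute risk difference for one or more major complications and 95% CI", followed by "linear regression for length of stay, physical function, and blood tests".

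The rest of the article describes what these outcomes are:

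- **Blood gases.** Point-of-care blood tests: "All of the randomized patients in group A at the UMC Utrecht will undergo blood tests". The purpose is given in the same section: "The goal of these POCT measurements is to present a curve of the gaseous changes during a dangling protocol". Table 3 lists, for each of postoperative days 7 to 12, flap and contralateral samples before a session and a flap sample at the end.
- **Complications.** Objectives: "We hypothesize that there is no difference in one or more major complications at 6 months". A matching hypothesis is stated for minor complications at 3 and 6 months. Neither has a margin. The analysis sentence gives a risk difference with 95% CI for major complications and does not name minor complications.
- **Physical function.** Trial design, after Fig. 1: patients complete "online questionnaires at 3 and 6 months and at 1, 1.5, and 2 years postoperative", which is five occasions per patient.

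**The concern.** The rule and the design do not match in two places.

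First, superiority in this trial means a comparison of the two randomised arms. Blood gases are not measured in group B, so no such comparison exists. The blood-gas data are samples nested within patients: flap against contralateral leg, before against after, over six days. The regression label is shared with length of stay, which is one value per patient, and says nothing of this nesting. At stake is whether the intervals around the intended curve have the right width.

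Second, a superiority test can reject equality but cannot establish it. The article handles this properly for the primary outcome, with a 12% margin and a confidence-interval rule. For complications it states a hypothesis of equality and then names a test that cannot support it. With few events expected, a non-significant result is likely even if complications rise materially, and the stated hypothesis makes that result easy to misread as reassurance on safety.

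**Working it through.** **The plan's own figure.** No figure is stated for the secondary analyses; the only one is the total of 130 for the primary comparison. With 6% in both arms, a 12-point margin, one-sided 2.5% and 80% power:

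n per arm = (1.960 + 0.842)² × 2 × 0.06 × 0.94 / 0.12² = 7.85 × 0.1128 / 0.0144 ≈ 61.5, so 62 per arm and 124 in total. Then 124 / 0.95 = 130.5, rounded up to 131, against 130 stated. The figure reproduces and this point does not touch it. Below, 65 per arm is 130 / 2, assuming 1:1 allocation (the ratio is not stated).

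**Blood gases: can the stated test be run?** The test needs values in groups A and B. Trial design and Point-of-care blood tests both restrict sampling to group A at one centre. No between-arm test is possible. This needs no assumption.

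**Blood gases: data structure.** Table 3 gives 3 samples × 6 days = 18 per patient, of which 2 × 6 = 12 are from the flap. The text of the section says "Blood will be taken from the free flap and the contralateral leg at the beginning and at the end of the dangling session", which read literally adds a contralateral sample at the end: 4 × 6 = 24. I use Table 3, so 18 is the lower count.

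**Blood gases: effect of ignoring the patient.** Let ρ be the within-patient correlation, taken as equal for all pairs. The article gives no value, so a range is assumed.

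- Mean flap level, 12 samples: true SE / reported SE = √(1 + 11ρ).
- Before/after change analysed without pairing: reported SE / true SE = 1 / √(1 − ρ).

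| ρ (assumed) | Mean level: SE too small by | Before/after: SE too large by |
|---|---|---|
| 0.2 | 1.79 | 1.12 |
| 0.5 | 2.55 | 1.41 |
| 0.8 | 3.13 | 2.24 |

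The two errors run in opposite directions.

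**Complications.** The article gives no major-complication rates, so these are assumed. Exact power at 65 per arm, two-sided 5%:

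| Assumed rates | Fisher | 95% CI excludes 0 (Newcombe) | 95% CI excludes 0 (Wald) |
|---|---|---|---|
| 3% v 9% | 16% | 25% | 34% |
| 3% v 6% | 4% | 8% | 15% |

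At 3% v 9% the expected Wald half-width is 1.96 × √(0.03 × 0.97/65 + 0.09 × 0.91/65) = 1.96 × 0.0413 ≈ 8.1 percentage points, against a true difference of 6 points. A tripling would be non-significant in 66% to 84% of such trials, depending on the method.

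**Physical function.** If the five visits were stacked and treated as independent, the arm-effect SE would be too small by √(1 + 4ρ): 1.48 at ρ = 0.3, 1.73 at 0.5 and 1.95 at 0.7. Type I error is 2 × [1 − Φ(1.96 / √(1 + 4ρ))] = 18.6%, 25.8% and 31.5%. A simulation with 62 per arm gave 18%, 26% and 32%. The same simulation with one visit analysed alone gave about 5%, so separate regressions per visit have no such error.

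**The case against.** The strongest reply is that much of the harm depends on an analysis the article does not describe. A reader might infer that ordinary regression will be run on pooled visits and that the standard errors for physical function are therefore wrong. The article does not say so. It says linear regression, and per-visit models fit that wording equally well and are valid. An article condenses a fuller protocol, and the handling of repeated measures is commonly left to the analysis plan. This stands: the type I error figures for physical function are conditional on pooling and are not a fault shown in the plan. Nor does the repeated-measures point apply to length of stay.

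On blood gases, one can say that the single-arm design is explicit, that nobody could run a between-arm test by mistake, and that regression on day can describe a curve. That limits the harm, but the stated rule still names a test that cannot be done and does not match the stated aim.

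On complications, a reader might infer that a non-significant result will be declared proof of no difference. No section says that. The risk difference with 95% CI is already planned for major complications, which is the right summary. Fisher's test is named only for the interim analysis, so the Fisher power understates what the planned interval would achieve, and the range above is the fair statement. What remains is that the hypothesis as worded, without a margin, cannot be supported by the test as named.

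**Conclusion.** The point holds on two counts that rest on the text alone. Blood gases cannot be tested for superiority between arms, because only group A at one centre is sampled and the aim is a within-patient curve. The no-difference hypotheses on complications have no margin, and a superiority test cannot support them.

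The sizes are conditional. The blood-gas SE errors (1.8 to 3.1 times too small for mean level, 1.1 to 2.2 times too large for before/after change) assume a regression that ignores the patient and equal correlations of 0.2 to 0.8. The power of about 16% to 34% assumes 65 per arm and rates of 3% and 9%. Physical function is a matter of naming the model; it is not an established error. The primary test and the sample size are unaffected. The change is worth making because the affected outcomes include the comparison of major complications and the whole blood-gas substudy.

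**What to change.** 1. **Blood gases.** Remove them from the outcomes under "The secondary hypotheses will be tested for superiority". State that within-patient change is estimated in group A only, with a linear mixed model: random patient effect; fixed effects for sampling site, before/after and day. Reconcile Table 3 with the text on whether the contralateral leg is sampled at the end of a session.
2. **Complications.** Restate both objectives as estimation of the risk difference with 95% CI. This is already planned for major complications; extend it to minor complications. State that non-significance will not be reported as no difference.
3. **Physical function.** Name either a mixed model for repeated measures with arm, time and arm-by-time, or a separate regression at each visit.

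The cost is wording in the protocol and analysis plan and slightly more analysis work. No extra patients or data are needed.

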### Recruitment, consent, and withdrawal

Patients will be invited by a plastic surgery resident who is not affiliated with this study or clinically responsible for the patient. This will be done before POD 5. The patient will then have at least 24 h to decide whether he/she would like to join the study. The patient will be provided with an information letter and asked to give written informed consent. The study will start on POD 7. If a patient at the UMC Utrecht is randomized to group A and would like to take part in the study but does not want to have the POCT performed, then the patient will still remain in group A (without the blood test).

Based on the current literature, there are no known increased risks involved with participation in this study. The hypothesized beneficial effect is that patients in group B might have a shorter hospital stay.

Subjects can leave the study at any time for any reason if they wish to do so, without any consequences. The investigator can decide to withdraw a subject from the study for life-threatening medical reasons. If during the study it is anticipated that there is a very high risk of total flap necrosis, the treating physician can decide to withdraw the patient from the dangling part of the study. This applies to patients in both groups A and B. This risk will be an estimation based on the clinical experience of the surgeon. For ethical reasons, we believe that this possibility is important in this study. The patient will still be included for the secondary objectives. If a patient experiences an adverse event which prevents the patient from adequately performing a dangling or a non-dangling protocol, that patient will be terminated from the study for the primary study outcome. If possible, the patient will still be included for the secondary objectives.

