## Methods/design

### Trial design

The study is taking place at three Dutch hospitals: University Medical Center (UMC) Utrecht, Erasmus University Medical Center (Erasmus MC) Rotterdam, and UMC Groningen. A dangling protocol is the current standard of care in these hospitals. Patients are randomly assigned by a computer program to group A or B. Patients in group A start a dangling protocol on POD 7. Patients in group B can mobilize without limitations starting on POD 7 and are discharged from the hospital when possible. All patients will be seen on POD 12–15, after 5–7 weeks, 2.5–3.5 months, and 5–7 months at the ward or the outpatient clinic. During these visits the complications will be evaluated. The study phases and data collection time points are shown in Fig. 1. The Standard Protocol Items: Recommendations for Interventional Trials (SPIRIT) checklist is provided as Additional file 1.

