### Sample size calculation

Based on the incidence of partial flap necrosis in the meta-analysis by Xiong et al., we performed a power calculation [8]. Because total free flap loss rarely occurs after POD 5, we decided to focus in this study on partial flap loss. Based on a rate of partial flap loss of 6%, we decided that an absolute increase in incidence of 12% would be clinically significant. To detect this non-inferiority margin with 80% power and a two-sided 95% confidence interval (CI) and 5% estimated loss to follow-up, we aim to include 130 patients. Each year about a hundred lower limb reconstructions are performed at our three hospitals, resulting in an inclusion time of 2 years.

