### Limitations

Given that this is a non-blinded study, patients who are randomized to the no-dangling group could implement a dangling protocol on their own. To prevent this, we will provide patients in this group with a step counter, and they will have to keep track of the amount of time that their leg was in a dangling position.

For ethical reasons, we believe that it is important that the treating physician can decide to withdraw a patient from the dangling part of the study if the physician thinks the risk of flap necrosis is too high. However, this could lead to treatment indication bias. However, we should be able to account for this by intention-to-treat or per protocol analysis.

Our sample size calculation is based on a rate of partial flap loss of 6%. We decided that a rather high absolute increase in incidence of 12% would be clinically significant. If we had chosen a lower increase of incidence the sample size would have increased significantly, resulting in a non-feasible study.

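### Randomised patients are dropped from the primary outcome after an adverse event, and by implication for high flap risk, which contradicts the intention-to-treat analysis and can bias the non-inferiority comparison.

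*Protocol article*

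**What the plan says.** Four statements in the Protocol article bear on who is counted in the primary analysis.

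- **Statistical analysis.** "We will perform an intention-to-treat analysis". The section adds a per protocol analysis, a baseline comparison of withdrawn and lost patients, and multiple imputation. Non-inferiority is declared if the upper 95% limit of the risk difference in partial flap loss (major and minor combined) is within 12%.
- **Recruitment, consent, and withdrawal, adverse-event rule.** If an adverse event keeps a patient from adequately following either regimen, "that patient will be terminated from the study for the primary study outcome". Such a patient is kept for the secondary objectives if possible.
- **Same section, high-risk rule.** If a very high risk of total flap necrosis is anticipated, "the treating physician can decide to withdraw the patient from the dangling part of the study". The rule covers both arms and rests on the surgeon's clinical estimate. The text keeps these patients for the secondary objectives and does not mention the primary one.
- **Limitations.** The article concedes that the high-risk rule could introduce bias by treatment indication, but answers that "we should be able to account for this by intention-to-treat or per protocol analysis".

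The Randomization section states that the trial is not blinded.

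**The concern.** Intention-to-treat means that every randomised patient contributes the primary outcome in the allocated arm. A rule that takes patients out of the primary outcome because of something that happened after randomisation cannot be followed at the same time. An unseen analysis plan could not fill this as a gap, because the article itself states two incompatible rules.

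The removals are unlikely to be neutral. One trigger is perceived danger to the flap. The other is an adverse event severe enough to stop the regimen, and flap problems could be among such events. Both judgements are made by people who know the allocation. If patients heading for flap loss are removed at similar rates in both arms, a true excess in the no-dangling arm shrinks towards zero. In a non-inferiority trial that makes a false positive conclusion more likely.

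The endpoint definitions make the effect visible. Study parameters classes partial flap loss as a minor or a major complication, and complications are secondary outcomes. A removed patient's partial flap loss could therefore be counted in a secondary analysis and left out of the primary one, which is about partial flap loss.

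**Working it through.** **1. The design figure.** Inputs from Sample size calculation: a partial flap loss rate of 6%, a margin stated as "we decided that an absolute increase in incidence of 12% would be clinically significant", and the target "with 80% power and a two-sided 95% confidence interval (CI) and 5% estimated loss to follow-up, we aim to include 130 patients". The allocation ratio is not given ("Patients are randomly assigned by a computer program to group A or B"), so 1:1 is assumed.

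n per arm = (1.960 + 0.842)² × 2 × 0.06 × 0.94 / 0.12² = 61.5, so 62 per arm and 124 in total. Allowing 5% loss gives 124 / 0.95 = 130.5, or 124 × 1.05 = 130.2. The planned 130 is reproduced, and the sample size is not in question here.

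**2. What removal does to the visible rates.** Suppose the true rates lie exactly at the margin: 6% with dangling (A) and 18% without (B). If a fraction f of would-be events is removed from numerator and denominator, the visible rate is

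q = p(1 − f) / (1 − pf).

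For f = 0.5 in both arms: q_A = 0.03 / 0.97 = 3.1%, q_B = 0.09 / 0.91 = 9.9%. The visible difference is 6.8 points instead of 12.

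**3. False non-inferiority rate.** This is the exact binomial probability that the upper Wald 95% limit lies below 12%, starting from 62 patients per arm, with each would-be event removed independently with probability f. The documents give no removal rate, so every f is an assumption.

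| Would-be events removed, A / B | Visible difference (points) | False non-inferiority |
|---|---|---|
| 0 / 0 | 12.0 | 3.6% |
| 10% / 10% | 11.1 | 5.1% |
| 25% / 25% | 9.6 | 9.2% |
| 50% / 50% | 6.8 | 26.6% |
| 0 / 25% | 8.1 | 13.2% |
| 0 / 50% | 3.9 | 40.9% |
| 25% / 0 | 13.4 | 2.2% |
| 50% / 0 | 14.9 | 1.3% |

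The first row exceeds the nominal 2.5% because of the Wald interval at this sample size. The comparison to make is with 3.6%.

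**4. How many patients that is.** Expected events in this scenario are 62 × 0.06 = 3.7 in A and 62 × 0.18 = 11.2 in B. Removing 25% of them means about 1 patient in A (0.9) and 3 in B (2.8).

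**5. If not every removed patient would have had an event.** Suppose 10% of each arm is removed, leaving 56 per arm. If removal is unrelated to outcome, the false rate is 3.8%, essentially unchanged. If the removed patients carry assumed event risks of 30% in A and 60% in B, the visible rates are (0.06 − 0.03) / 0.9 = 3.3% and (0.18 − 0.06) / 0.9 = 13.3%. The difference is then 10.0 points and the false rate 10.1%. The damage comes from removal that depends on outcome, not from the loss of numbers.

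**6. Whether the stated safeguards help.** Intention-to-treat protects only if these patients' primary outcomes are used, and the adverse-event rule says they are not. Per protocol leaves out patients who stopped their regimen, so it does not recover them. Multiple imputation, if applied to them, relies on observed data explaining why they are missing. That is doubtful when removal rests on a surgeon's impression of the flap.

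**The case against.** Five points can fairly be made on the other side.

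- **The high-risk rule does not mention the primary outcome.** This is correct. A reader might infer that the article states the removal of high-risk patients from the primary outcome. It states only withdrawal from the dangling part and retention for secondary objectives. Limitations, which addresses this group, even suggests they are analysed as randomised. Removal is the natural implication of the wording, but only the adverse-event rule is explicit.
- **If the intention-to-treat statement governs, nobody is lost.** This is also true, and because complications are assessed at the same visits, it is feasible. But the article does not say which statement governs, and the adverse-event rule names the primary outcome directly.
- **The direction is not fixed.** This stands. A reader might infer that the trial is biased towards non-inferiority. Removal is discretionary and open to both arms, and removal mainly from group A works the other way.
- **Removals may be few.** This stands in part. The trigger is risk of total necrosis, whereas the endpoint is partial loss. The article says total loss is rare after postoperative day 5, and the study starts on day 7. Re-intervention patients are kept in the study. At 10% removal from both arms the change is modest (5.1% against 3.6%). None of this limits the adverse-event rule, which has no such trigger.
- **Event counts must not be mixed.** About 4 events per arm is the design case of 6% in both arms. It cannot support a claim that a handful of removals decides the result when the rates are 6% and 18%, where about 11 events are expected in group B.

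**Conclusion.** The contradiction is real and should be corrected. The adverse-event rule cannot coexist with intention-to-treat, the wording of the high-risk rule implies the same exclusion, and the assurance in Limitations does not hold for patients whose primary outcome is not used.

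The supportable statement on bias is that these exclusions can distort the comparison. The most plausible direction is towards non-inferiority if they fall equally on both arms or mainly on group B, and the opposite if mainly on group A. The false non-inferiority rates range from 1.3% to 40.9% across the assumed patterns, against 3.6% with no removal. They rest on assumed removal fractions, 1:1 allocation, 62 evaluable patients per arm, true rates of 6% and 18%, and a Wald interval. They illustrate sensitivity and do not forecast how often removal will occur. The case for change rests on the contradiction itself, not on the larger scenarios.

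**What to change.** Reconcile the three sections as follows.

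- **Recruitment, consent, and withdrawal:** delete the removal from the primary outcome in the adverse-event rule. State for both rules that the patient remains in the primary analysis. Leave the physician's discretion to stop the regimen as it is.
- **Statistical analysis:** state that every randomised patient is analysed in the allocated arm, with partial flap loss counted to 6 months whether or not the regimen was followed. Restrict multiple imputation to outcomes that are truly missing. Keep per protocol as a supporting analysis. Requiring it to meet the margin as well would make it co-primary and would not bring back the removed patients, so that is not asked for here.
- **Limitations:** replace the claim that either analysis accounts for the bias. Only an analysis that uses these patients' outcomes does so.

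The cost is mainly wording. Complications are already evaluated at visits up to 5–7 months. Some added effort is needed to record the primary outcome in patients who stop their regimen, particularly the adverse-event group, whose retention is currently only if possible.
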